### Strategies to improve adherence

Firstly, before enrollment, we repeatedly confirm the participants’ willingness and compliance with the study’s requirements. Secondly, dedicated researchers will be responsible for monitoring the intensity and frequency of the participants’ weekly exercise through the *Polar Flow for Coach* system, and they will repeatedly remind and guide them to complete the 12-week training plan as required. At the same time, the researchers will maintain contact with the participants over the 12 weeks and collect their daily dietary records. Thirdly, participants will receive a supermarket voucher valued at HK$200 upon completion of the intervention.

### Data analysis

An intention-to-treat (ITT) analysis will be conducted as our primary analytical approach to evaluate the overall effectiveness of the intervention. Additionally, a per-protocol analysis will be performed as a sensitivity analysis, which will only include participants who met the predefined adherence criteria. Missing data will be addressed using the Multiple Imputation by Chained Equations (MICE) technique. The normality of the data will be assessed using the Shapiro-Wilk test, and Levene’s Test will be used to assess the homogeneity of variances. Continuous variables will be presented as means with standard deviations (SD) or medians with interquartile ranges (IQR), depending on their data distribution. Categorical variables will be presented as frequencies and percentages. Baseline characteristics among the three groups will be compared using a One-way Analysis of Variance (ANOVA) for normally distributed continuous variables, a Kruskal-Wallis H test for non-normally distributed continuous variables, and Chi-square tests for categorical variables.

To test the main hypothesis, the primary outcome is defined as flicking capacity. Generalized Estimating Equations (GEEs) will be used to determine the group-by-time interaction effect for both the primary and secondary longitudinal outcomes. To rigorously specify the GEE models, the distributional family and link function will be selected based on the specific nature of each outcome variable. An exchangeable working correlation structure will be specified to account for the within-subject correlation of repeated measures across time points. Furthermore, robust standard errors (the sandwich estimator) will be utilized to ensure valid statistical inference even if the working correlation structure is misspecified.

Furthermore, changes in monitored lifestyle variables (i.e., dietary intake, physical activity, and sleep quality) over the intervention period will be evaluated. If any of these variables exhibit significant changes or between-group imbalances, they will be incorporated as covariates in the GEE models to adjust for potential confounding effects, thereby isolating the true effect of the exercise interventions.

The primary outcome will be tested at a two-sided α level of 0.05. For the secondary outcomes, the resulting *p*-values for the group-by-time interaction effects derived from the GEE models will be adjusted using the Benjamini-Hochberg False Discovery Rate (FDR) method. If significant main or interaction effects are detected in the GEE model, simple effect analyses and post-hoc pairwise comparisons will be performed within the GEE framework using estimated marginal means with a Bonferroni adjustment.

Prior to investigating potential associations, we will first test for true inter-individual differences in response to the intervention by comparing the variance of the change between the groups [99]. If true inter-individual variability is confirmed, Pearson’s or Spearman’s rank correlation coefficients will be utilized, as appropriate, to investigate potential associations between esports performance indicators and hand correlates, body composition, and physical competence. To account for multiple testing in these correlation analyses, p-values will be adjusted using the Benjamini-Hochberg FDR method.

All statistical analyses will be conducted using R software (version 4.4.2). A two-sided *p*-value of < 0.05 will be considered statistically significant. To indicate the precision of the estimates, 95% confidence intervals (CIs) will also be calculated and reported.

For the exploratory qualitative component, all semi-structured interviews will be audio-recorded and transcribed verbatim. The transcripts will be analyzed using thematic analysis, facilitated by NVivo 12 software, to identify, analyze, and report recurring themes within the participants’ subjective experiences. Although the sample size is fixed by the intervention design, we will continuously monitor for thematic saturation during this data analysis phase. Rather than formally merging these findings with the quantitative data in a mixed-methods matrix, the qualitative themes will be utilized during the interpretation phase to contextualize the objective performance outcomes. This approach will provide a deeper understanding of the participants’ perspectives and assist in elucidating the potential underlying mechanisms between aerobic exercise and esports performance.

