**Methods:**

In this three-arm randomized controlled trial, 195 FPS gamers (aged 18–29) will be randomly assigned to HIIT, MICT, or control groups. Interventions consist of three weekly sessions for 12 weeks (HIIT: 10 × 1-minute high-intensity bouts interspersed with 1-minute active recovery; MICT: 20-minute continuous moderate-intensity exercise). The primary outcome is flicking capacity (a core metric of esports performance). Secondary outcomes include other gaming operational metrics, esports-related psychological skills, body composition, and physical competence. All outcomes will be assessed at baseline, post-intervention (12 weeks), and follow-up (16 weeks).

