### Experimental design

This study is designed as a three-arm randomized controlled trial. Given the limited number of longitudinal studies examining exercise interventions in esports, our sample size estimation was informed by the results of existing acute or short-term exercise studies aimed at enhancing esports performance, alongside preliminary data from our previous research [27,35]. Based on the effects of exercise on esports performance reported in these studies, we conservatively estimated a moderate effect size (d = 0.4) to power our primary outcomes (esports performance). Power analysis conducted via G*Power indicated that a minimum sample of 52 participants per group would be required to detect significant effects with 80% power (α = 0.05). Accounting for an anticipated dropout rate of 20%, 65 participants for each group will be recruited for this study. In total, we will recruit 195 participants, and they will be randomly allocated into three groups (1:1:1): HIIT, MICT, and a control group. To prevent baseline imbalances in variables relevant to gaming performance, a stratified block randomization procedure will be employed. Participants will be stratified into two strata based on their years of FPS gaming experience (e.g., above vs. below the median years of experience of the recruited cohort). Within each stratum, participants will be randomly allocated to the HIIT, MICT, or control group in a 1:1:1 ratio using randomly permuted blocks. The randomization sequence will be generated by an independent researcher using a computer-based random number generator (Research Randomizer) to ensure allocation concealment. The entire allocation process will be conducted by a staff member who will not be participating in the study. In scenarios requiring assessors to utilize measurement tools for evaluating metrics, we engage testers who are completely blind to the participants’ group assignments to conduct the assessments. For metrics tested via computer, our assessors serve merely to facilitate and oversee the process, with the computer’s saved data serving as the definitive record to ensure data objectivity. This approach has been proven reasonable in the past esports performance assessment [27]. The intervention groups will receive a 12-week HIIT or MICT exercise program, while the control group will not receive any intervention. All groups will report their dietary intake, physical activity, sleep patterns, and gaming activity. All participants will undergo a baseline test, followed by an immediate post-test at the end of the 12-week intervention period and a follow-up test 4 weeks after the intervention ends. Fig 2 illustrates the specific experimental procedure.

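### The primary group-by-time GEE treats the baseline score as an outcome instead of conditioning on it, so its contrasts are change-type: unbiased, but generally less precise than a baseline-adjusted analysis

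*Protocol article*

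**What the plan says.** The Data analysis section of the protocol fixes the endpoint ("To test the main hypothesis, the primary outcome is defined as flicking capacity") and the test: "Generalized Estimating Equations (GEEs) will be used to determine the group-by-time interaction effect for both the primary and secondary longitudinal outcomes". The Abstract (Methods) gives the time points: "All outcomes will be assessed at baseline, post-intervention (12 weeks), and follow-up (16 weeks"). Experimental design agrees: "All participants will undergo a baseline test, followed by an immediate post-test at the end of the 12-week intervention period", with a further test four weeks later.

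Other features of the model in Data analysis:

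- Correlation: "An exchangeable working correlation structure will be specified to account for the within-subject correlation of repeated measures across time points", with sandwich standard errors.
- Family and link are left open: "the distributional family and link function will be selected based on the specific nature of each outcome variable".
- Covariates are the monitored lifestyle variables, entered conditionally: "If any of these variables exhibit significant changes or between-group imbalances, they will be incorporated as covariates in the GEE models". The Intervention section adds that indoor or outdoor setting will be considered as a covariate.
- Missing data are multiply imputed.
- Level: "The primary outcome will be tested at a two-sided α level of 0.05".

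The baseline flicking score does not appear among the covariates, and no constraint on the baseline means is stated.

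**The concern.** For group-by-time to be the test of treatment, baseline has to be one of the levels of time. If only weeks 12 and 16 were outcomes, that term would ask whether the arms' difference shifts between those two visits. A group-by-time model over three visits, with no further qualification, fits a separate mean in each of the nine arm-by-visit cells, including three baseline means that randomisation makes equal in expectation. The treatment contrast then subtracts the whole observed baseline difference, when the efficient amount to subtract is the part that predicts the later score.

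The exchangeable working correlation does not repair this. When every cell has its own mean and the data are complete, the fitted means are the cell means whatever correlation is assumed.

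What is at stake is precision, on the primary outcome and on each secondary outcome analysed the same way. It matters because the stated sample size has little slack (see the working).

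**Working it through.** **The plan's own figure.** Experimental design gives d = 0.4, 80% power, alpha 0.05 and 52 per group, raised for 20% dropout to 52/0.8 = 65.

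- A two-sided, two-sample t-test at d = 0.4 needs 100 per group. With 52 per group its power is 52%.
- A one-sample or paired t-test at d = 0.4 gives exactly 52 (power 0.808; 51 gives 0.7999).
- A comparison between arms reaches about 52 only with a correlation that the protocol does not state: about 0.74 for change scores, since 2(1 - 0.74) = 0.52, or about 0.69 with baseline adjustment, since 1 - 0.69² = 0.524.

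So whether 52 per arm suffices depends on rho and on how baseline is used.

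**What the stated model estimates.** A saturated group-by-time GEE with exchangeable correlation and identity link was fitted to complete simulated data (3 arms, 3 visits, 52 per arm). The week-12 interaction coefficient equalled the raw difference in mean change: 0.004439 in both at rho 0.5, and -0.151417 in both at rho 0.8. With a Poisson family and log link it equalled the log of the ratio of the arms' follow-up-to-baseline mean ratios (0.0915 in both). The baseline means remain free under either link.

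**Variance.** Let rho be the correlation of baseline with follow-up and k the ratio of follow-up SD to baseline SD. In units of the baseline variance, per arm:

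- change contrast: 1 + k² - 2·rho·k
- baseline-adjusted contrast: k²(1 - rho²)
- difference: (1 - rho·k)², which is never negative.

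With k = 1 these become 2(1 - rho) and 1 - rho². Their ratio is (1 + rho)/2 and the saving is (1 - rho)/2. The protocol gives neither rho nor SDs, so the values below are assumptions. Power is for one two-arm comparison (noncentral t, d = 0.4 in single-visit SD units, 52 per arm, two-sided 0.05).

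| rho | change | adjusted | variance saved | SE saved | power, change | power, adjusted |
|---|---|---|---|---|---|---|
| 0.3 | 1.40 | 0.91 | 35% | 19% | 40% | 56% |
| 0.5 | 1.00 | 0.75 | 25% | 13% | 52% | 65% |
| 0.7 | 0.60 | 0.51 | 15% | 8% | 74% | 81% |
| 0.8 | 0.40 | 0.36 | 10% | 5% | 89% | 92% |
| 0.9 | 0.20 | 0.19 | 5% | 3% | 99% | 100% |

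**Unequal SDs.** At rho = 0.8 and k = 1.2 the change factor is 1 + 1.44 - 1.92 = 0.52 and the adjusted factor is 1.44 × 0.36 = 0.518. The saving is (1 - 0.96)²/0.52 = 0.3%. At k = 1.3 it is again about 0.3%.

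**The omnibus test.** With three arms and three visits the interaction has (3 - 1)(3 - 1) = 4 degrees of freedom, so the two-arm figures are not its power. Suppose one arm differs from the other two by 0.4 SD at both follow-up visits, with equal SDs and exchangeable correlation. Noncentral chi-square power for the interaction is then 57%, 81% and 95% at rho 0.5, 0.7 and 0.8. A 4-df baseline-adjusted joint test gives 77%, 90% and 97%.

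**The case against.** The strongest reply is that the article gives the method, the tested term, the correlation and the standard errors, but not the mean model, and that a fuller analysis plan may hold a common-baseline constraint. This stands in part: separate baseline means are the natural reading, not a stated fact. But the tested term is stated, and the covariates that are named do not include the baseline score.

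Second, this is efficiency, not error. That stands. A reader might infer that chance baseline imbalance biases the analysis through regression to the mean. Imbalance affects the estimate given the baseline that happens to occur, but over randomisations the change contrast is unbiased.

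Third, a reader might take a 10–25% loss as established. It is not: that range is the variance saving for assumed rho of 0.8 down to 0.5 with equal SDs. If baseline predicts follow-up very strongly, rho is high and the gain is at its smallest.

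Fourth, a reader might call the primary estimate a raw difference in change without qualification. The outcome is a count and the link is open, and added covariates would end the exact identity.

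Fifth, constraining the baseline means to be equal might seem interchangeable with adjustment. It is when the working covariance is about right. In a simulation with rho 0.8 and a follow-up SD 1.2–1.3 times baseline, the constrained GEE with exchangeable correlation had 3–9% more variance than the change contrast, while baseline adjustment was about equal to it.

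**Conclusion.** The point holds as one of precision. Read naturally, the primary GEE gives change-type contrasts and forgoes information in a baseline score that every participant provides. Baseline adjustment is, in large samples, never less precise. Its gain is large if rho is moderate, small if rho is near 0.9, and can be close to nil if the SD grows after baseline at high rho. No single percentage can be quoted from the protocol, since it gives no correlation or SDs. Around rho 0.7 with equal SDs, the choice decides whether a two-arm comparison at 52 per arm passes 80%. The change is worth making, but the analysis as planned is not invalid.

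**What to change.** Fit the primary GEE to the week-12 and week-16 flicking scores, with arm, time, arm-by-time, baseline flicking capacity and baseline-by-time. Restate the primary test as the arm effect at week 12, or as arm and arm-by-time tested jointly. Arm-by-time alone must not remain the primary test, because in this model it compares the arms' difference at week 12 with that at week 16.

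Use the same form for each secondary outcome with its own baseline, and apply the false discovery rate adjustment to the matching arm-effect p-values.

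The cost is modest: no extra visits or participants, but the tested term in Data analysis must be reworded for both primary and secondary outcomes, which is more than a line of code. It should be done before any outcome data are examined by arm.

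### The plan relies on the sandwich estimator for valid inference but names no finite-sample correction; used in its ordinary form with a chi-square test, it would put the primary group-by-time test at about 6.2–6.6% instead of 5%

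*Protocol article*

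**What the plan says.** All points are in the protocol article.

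- **Model (Data analysis).** "Generalized Estimating Equations (GEEs) will be used to determine the group-by-time interaction effect for both the primary and secondary longitudinal outcomes". The working correlation is fixed: "An exchangeable working correlation structure will be specified to account for the within-subject correlation of repeated measures across time points".
- **Variance (Data analysis).** "robust standard errors (the sandwich estimator) will be utilized to ensure valid statistical inference even if the working correlation structure is misspecified". Neither the variant of the sandwich nor the reference distribution of the test is given.
- **Level (Data analysis).** "The primary outcome will be tested at a two-sided α level of 0.05".
- **Visits (Abstract, Methods).** "All outcomes will be assessed at baseline, post-intervention (12 weeks), and follow-up (16 weeks").
- **Size (Experimental design).** "a minimum sample of 52 participants per group would be required to detect significant effects with 80% power (α = 0.05"), and "Accounting for an anticipated dropout rate of 20%, 65 participants for each group will be recruited for this study". There are three arms, allocated 1:1:1.
- **Missing data (Data analysis).** The primary approach is intention-to-treat with multiple imputation by chained equations. How the multi-degree-of-freedom test is pooled over imputations is not described.

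**The concern.** The sandwich estimator is consistent even when the working correlation is wrong, but consistency is a large-sample property. At a finite size two further errors arise, and neither has anything to do with the correlation structure.

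1. The plain sandwich is biased downward. In a saturated group-by-time model it divides each arm's residual cross-products by n where an unbiased estimate would divide by n − 1.
2. A chi-square Wald reference treats the estimated covariance matrix as known. The cost of that grows with the number of parameters tested together.

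With three arms and three categorical visits the interaction has (3 − 1) × (3 − 1) = 4 degrees of freedom, and both errors push towards rejection. At stake is whether the one test assigned the 5% level holds it. The secondary interaction p-values passed to the false discovery rate step come from the same model and would share the small bias.

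**Working it through.** **Inputs from the protocol article.** Three arms; visits at baseline, week 12 and week 16; two-sided 0.05; 52 per arm evaluable and 65 recruited (52 / 0.8 = 65).

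**Assumptions, because the article does not give them.** Uncorrected sandwich; chi-square reference; time categorical; identity link; complete data; no covariates; within-person correlation 0.6 or 0.7. First-order autoregressive truth, overdispersed counts and unequal numbers of completers were run as variations.

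**Test statistic.** For arm k, take each person's two changes from baseline, with mean vector m_k, and

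V_k = Σ (c_i − m_k)(c_i − m_k)′ / n².

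Let h stack (m_HIIT − m_control) and (m_MICT − m_control). Its covariance C has diagonal blocks V_HIIT + V_control and V_MICT + V_control, and off-diagonal blocks V_control. Then W = h′C⁻¹h. With complete data and a saturated mean model this equals the Wald statistic of the exchangeable GEE with robust covariance. Two data sets fitted both ways agreed (3.9741 and 5.4673).

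**Stated level.** The nominal test rejects when W > 9.488, the 95% point of chi-square on 4 df. That is a 5% test only if C is known.

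**Type I error under the null** (100,000 to 300,000 simulated trials per setting; Monte Carlo standard error 0.04 to 0.08 points):

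| Setting, plain sandwich, chi-square | 52 per arm | 65 per arm |
|---|---|---|
| Normal, exchangeable (several runs) | 6.4–6.6% | 6.1–6.3% |
| Normal, autoregressive truth | 6.6% | 6.2% |
| Overdispersed counts | 6.5–6.6% | 6.1–6.3% |
| Unequal completers 46/48/62 | 6.6% (156 in total) | – |
| Single 1-df interaction contrast | 5.3–5.6% | 5.2–5.5% |

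The rate is nearly the same under exchangeable and autoregressive truth. So the excess comes from estimating the covariance, not from misspecifying the correlation.

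**With multiple imputation.** One plausible version gave 6.0% (20,000 runs, standard error 0.17 points). It used 65 per arm, 20% dropout at random, correlation 0.7, 20 imputations, the plain sandwich, and a pooled Wald test with an F reference.

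**Effect of corrections.** In this balanced setting Kauermann-Carroll multiplies W by (n − 1)/n and Mancl-DeRouen by ((n − 1)/n)². The latter is (51/52)² = 0.962 and (64/65)² = 0.969. With N = 156 or 195, F(4, N − 3) raises the critical value of W from 9.488 to 9.723 (153 denominator df) or 9.675 (192).

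| Correction | 52 per arm | 65 per arm |
|---|---|---|
| Kauermann-Carroll, chi-square | 6.1% | 5.8–5.9% |
| Mancl-DeRouen, chi-square | 5.7% | 5.5% |
| Kauermann-Carroll, F(4, N − 3) | 5.6–5.7% | 5.4–5.5% |
| Mancl-DeRouen, F(4, N − 3) | 5.1–5.3% | 5.0–5.2% |

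**Power cost.** Find the noncentrality of a 4-df chi-square that gives a chosen power at the inflated level, then recompute power at the corrected level. Moving from 6.54% to 5.26% (52 per arm) and from 6.11% to 5.04% (65 per arm):

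- 90% power becomes 88.2% and 88.5%;
- 80% becomes 77.2% and 77.6%;
- 50% becomes 46.1% and 46.6%.

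The loss is about 1.5 to 4 points. Part of it is simply the power that an inflated level had bought.

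**The case against.** The case against has four parts.

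1. **Neither the uncorrected form nor the chi-square reference is in the text.** Bias-corrected versions are also sandwich estimators, and a condensed article may leave the variant to the analysis plan. This stands as far as it goes: the rates are conditional, and the absence of the detail alone would be no finding. The point survives because the article attaches an assurance of validity to an estimator named without qualification, and the unqualified term ordinarily means the uncorrected form.

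2. **The quoted sentence is correct on its own subject.** This stands. A reader might infer that the article's robustness claim is false, and the documents do not support that: the simulations show that a wrong working correlation adds essentially nothing. Only the strength of the assurance is at issue.

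3. **The simulated test is not the planned analysis.** The plan has imputation, possible covariates, and a family and link chosen per outcome. This stands in part. A reader might infer that an error rate above 6% is a fixed property of the plan, and it is not. The imputation version still gave 6.0%, so the excess does not disappear by that route.

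4. **The effect is immaterial.** With 156 to 195 independent participants the excess is small, and the single contrasts that carry the estimates and intervals are nearly unaffected. This stands as a limit on importance. A reader might infer that the confidence intervals or secondary p-values are materially wrong; the 1-df figures do not bear that out.

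**Conclusion.** The point holds in conditional form and is minor. Followed in the ordinary way (uncorrected sandwich, chi-square Wald test, categorical time), the primary omnibus test would reject a true null in about 6.2–6.6% of complete-data trials at 65 to 52 per arm. That is 1.2 to 1.6 points above the stated level, or 24% to 32% in relative terms (1.2/5 and 1.6/5). The size hardly depends on the assumed correlation or outcome distribution. It does depend on the unstated variant, the reference distribution and the pooling method. The trial's conclusions are not threatened, unless the primary p-value falls close to 0.05.

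**What to change.** In the second paragraph of Data analysis, make two changes.

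1. State that the GEE covariance will be a Mancl-DeRouen-type bias-corrected sandwich, with an F reference for the group-by-time test and t references for contrasts, and that both will be carried through the pooling over imputations.
2. Limit the validity claim to misspecification of the working correlation.

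Both parts of the first change are needed. Correcting the covariance but keeping chi-square, or using Kauermann-Carroll with F, restores the level only partly.

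**Cost.** A sentence or two and a choice of R package. For a contrast of two equal arms the standard error grows by n/(n − 1), which is 52/51 = 1.020 or 65/64 = 1.016. The t quantile adds under 1% (about 1.976 or 1.972 against 1.960), so intervals widen by roughly 2 to 3%. Omnibus power falls by about 1.5 to 4 points. Settling this before the data are analysed also removes a discretionary choice that could matter for a borderline primary result.
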